### Randomization

The study statistician generated and administrated 1:1 allocation randomization arrangement for the 5 study hospitals. Patients will be randomly assigned to group A (decompressive laparotomy with temporary abdominal closure) or group B (percutaneous puncture with placement of abdominal catheter) as shown in the flow-chart (Figure 1.). We did not stratify hospitals by procedure-volume or teaching status since all hospitals are under supervision of Medical Faculty of University of Belgrade, and the assumption is that hospitals are similar.

**Figure 1 F1:**
[figure not shown]
Flowchart with plan of randomization

### Statistical analysis

The analysis will be performed on the basis of an intention to treat (ITT) population and with respect to ITT principles.

The primary analysis consists of a comparison of the mortality rate during the hospital stay for acute pancreatitis in both treatment strategies. The comparison will be expressed in terms of relative risk and 95% confidence intervals. The research hypothesis will be evaluated by Fisher's exact test or Hi-square test (where appropriate), with a two-sided 0.05 significance level. In addition, survival probabilities over time will be estimated by Kaplan-Meier method and groups will be compared using the long-rank test.

Secondary endpoints as duration time of organ failure, intensive care and total hospital stay will be evaluated by t-test, while complication rates will be evaluated by Fisher's exact test or Hi-square test (where appropriate), also with a two-sided 0.05 significance level.

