### Treatment and monitoring before the randomization

All patients with AP will be treated according to pre-established treatment protocol. The treatment protocol for patients with predicted SAP comprising: enteral nutrition preferably via a nasogastric route (in case of intolerance nasojejunal tube will be inserted), an early endoscopic retrograde cholagiopancreatography (ERCP) with sphincterotomy in patients with obstructive cholangitis and/or jaundice and antibiotic prophylaxis. If gastrointestinal nutrition is contraindicated, the patients will receive parenteral nutrition. Patients with predicted mild form of disease will be treated with intravenous fluid and analgetics with close monitoring of vital signs, renal and pulmonary function. Intraabdominal pressure will be monitored routinely on daily basis in all patients with predicted SAP, represented by at least one of the following criteria: APACHE II score ≥ 8, Imrie score ≥ 3 points and CRP ≥ 150 mg/L. In addition, in all patients with clinically suspected intraabdominal hypertension, abdominal pressure will be also measured daily. In all patients who have diagnosed IAH or predicted SAP, SOFA score will be calculated daily. It is well known that, usually abdominal compartment syndrome develops in the very early course of disease (during the first week) and the we expect that vast majority of our patients will be recruited within that time frame. Although, if there will be patients with ACS in later course it will not be an exclusion criteria. Since, many patients will be transferred from referring centres, violation of pre-randomization protocol is not an exclusion criteria.

Intravesical pressure, which indirectly reflects IAP, will be measured using a standard technique that has been described by Cheatham et al. [26] Contrast enhanced CT (CCT) will be done in all patients with IAH, immediately after the diagnosis has been established. This diagnostic toll will be also performed after 7-10 days an all patients with predicted SAP.

Patients with abdominal compartment syndrome will be randomised either for decompressive laparotomy with temporary abdominal closure or percutaneous puncture with placement of abdominal catheter.

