### Sample size calculation

The sample size calculation is based on equivalence design for the primary endpoint- mortality rate of patients with abdominal compartment syndrome during acute pancreatitis. It is anticipated that decompressive laparotomy with temporary abdominal closure will lead to a mortality rate reduction from 60% of patients to 40%. Therefore, the expected reduction in mortality that was used for sample size calculation is 20%. With calculated 80% power of the study (beta error 0.20) and alpha error of 0.05 (two-sided) complete data from 47 patients per group will be necessary to demonstrate this effect, if it truly exists. Taking into account a 7% loss-to-follow up, a total of 2 × 50 patients have to be randomized.

Reported annual rate of treated patients with severe form of acute pancreatitis is about 250 (based on hospital data of Emergency Centre, Clinical Centre of Serbia, 3 affiliated hospitals of School of Medicine University of Belgrade and Military Academy), while the prevalence of abdominal compartment syndrome in this patient population is about 20%. Consequently, the total expected number of patients with abdominal compartment syndrome during acute pancreatitis in these 5 centres is about 50, annually. Based on this assumption, the expected study inclusion period would be ended in two years.

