## Conclusions

Currently, there are no prospective randomized trials in patients with ACS during SAP. There are several reasons including: low incidence, low hospital volumes with patients with AP, individualised treatment approach and very heterogeneous type of disease. Therefore we have planned this multicenter study in one city which serves a region of 3 million inhabitants. With a very similar treatment algorithm, these centres easily adapted their practice to the protocol for this study.

The final version of study protocol was approved by Ethical Committee Clinical Center of Serbia on 9^th ^of June, 2010.

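### The primary mortality comparison is unadjusted although SOFA is recorded daily before randomisation; the test is valid but gives up precision

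*Protocol article*

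**What the plan says.** The Statistical analysis section of the protocol article fixes the primary analysis as a comparison of in-hospital mortality by intention to treat: "The comparison will be expressed in terms of relative risk and 95% confidence intervals". The test is Fisher's exact or chi-square at a two-sided 0.05 level. Kaplan-Meier curves with a log-rank test are added. None of these names a covariate or a stratum.

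Three other places bear on that choice.

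- Treatment and monitoring before the randomization: "In all patients who have diagnosed IAH or predicted SAP, SOFA score will be calculated daily". Intra-abdominal hypertension (IAH) is part of the entry definition, so a SOFA value from before randomisation should normally exist.
- Conclusions: among the reasons why randomised trials are lacking, the article lists "individualised treatment approach and very heterogeneous type of disease".
- Randomization: a 1:1 arrangement was generated for the five hospitals, and "We did not stratify hospitals by procedure-volume or teaching status since all hospitals are under supervision of Medical Faculty of University of Belgrade". The hospitals are assumed to be similar. No severity factor is named for the allocation.

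**The concern.** Baseline severity is likely to vary widely in this trial. Under the Inclusion criteria and Table 1, a patient may enter with one, two or three failing organs. Late cases and patients transferred after departures from the pre-randomisation protocol are also accepted. If SOFA predicts death in these patients, a crude two-by-two comparison leaves explainable variation in the error term. The treatment effect is then estimated less precisely than the collected data allow.

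Precision matters more than usual here because, as shown below, the planned numbers give about half the power one would want, not the stated 80%. The choice also has to be made in advance. A severity-adjusted result added after a borderline crude result would look data-driven.

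**Working it through.** **1. The plan's own figure.** The inputs are in the Sample size calculation section: "With calculated 80% power of the study (beta error 0.20"; "alpha error of 0.05 (two-sided"; a treatment that "will lead to a mortality rate reduction from 60% of patients to 40" percent; and "complete data from 47 patients per group will be necessary to demonstrate this effect". With p1 = 0.60, p2 = 0.40 and mean 0.50:

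- n per group = [1.960·√(2·0.5·0.5) + 0.842·√(0.24 + 0.24)]² / 0.20² = (1.386 + 0.583)² / 0.04 = 3.877 / 0.04 ≈ 97.
- With unpooled variance: 0.48·(1.960 + 0.842)² / 0.04 ≈ 94.2, so 95.

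The stated 47 per group is not reproduced. One-sided, continuity-corrected, arcsine, non-inferiority and equivalence formulas for two arms all give 75 or more.

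**2. Power of the crude test as planned.** Power = Φ{[0.20 − 1.960·√(0.5/n)] / √(0.48/n)}.

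- n = 47: (0.20 − 0.2022) / 0.1011 = −0.02, so 49%.
- n = 50: (0.20 − 0.1960) / 0.0980 = 0.04, so 52%.
- Exact enumeration: chi-square 49% at 47 and 54% at 50; Fisher 41% and 46%.

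**3. What adjusting for one severity score adds.** The article gives no prognostic strength for SOFA, so the AUC for death is an assumption, shown as a range. In simulated trials, marginal mortality was held at 60% against 40%, the score was standard normal, and a logistic likelihood-ratio test was set against the uncorrected chi-square test.

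| Per group | Assumed AUC | Chi-square | Adjusted logistic | Gain (points) |
|---|---|---|---|---|
| 50 | 0.70 | 54% | 58% | 4 |
| 50 | 0.76 | 53% | 61% | 8 |
| 50 | 0.81 | 53% | 65% | 12 |
| 47 | 0.63 | 48.9% | 51.4% | 2.5 |
| 47 | 0.70 | 48.8% | 54.7% | 5.9 |
| 47 | 0.76 | 49.7% | 59.2% | 9.5 |
| 47 | 0.81 | 49.9% | 64.6% | 14.7 |

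A second set of runs at 50 per group gave 57%, 61% and 65% at AUC 0.69, 0.75 and 0.79, against 54 to 55% for chi-square. At the lower end that is a gain of 2 to 3 points. The gain is smaller at 50 than at 47 partly because the chi-square test is slightly liberal at 50: its exact null rejection rate at 50% mortality is 5.7%, against 4.9% at 47. The cautious summary is therefore 3 to 12 points.

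**4. If the score is useless.** At 50 per group the logistic test had 54% power against 55% for chi-square, a loss of about 1 point. A test based on the standardised log relative risk loses about 6 points.

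**5. Hospital.** With five hospitals of about equal size and 47 per group, the Cochran-Mantel-Haenszel test against chi-square gave 48% v 50% with no hospital effect, 50% v 50% at an assumed between-hospital SD of 0.3 on the logit scale, 52% v 51% at 0.6, and 56% v 52% at 1.0. The change is about −2 to +4 points.

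**6. Validity and chance imbalance.** Null rejection by the crude chi-square test was 4.6 to 5.6% in the severity simulations at 47 per group. At 50 per group the SD of a standardised baseline difference is √(2/50) = 0.2, so an absolute difference above 0.3 has probability P(|Z| > 1.5) = 13%.

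**The case against.** The strongest reply is that nothing here is an error. A relative risk with a chi-square or Fisher test is a valid analysis of a randomised trial, its p-value and interval already allow for chance imbalance, and the choice of an adjusted primary analysis is a matter of preference. The first two parts stand. A reader might infer that imbalance in severity invalidates the crude result; the null rejection rates show that it does not. The case for change is precision alone. It remains because the stated primary test sets aside a score that the protocol already has collected.

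Second, the AUC range is assumed. Entry already requires organ dysfunction, which may narrow the spread of SOFA, and the severity links cited in the Background are with IAH, not with death among patients who have the syndrome. This stands, and is why the range and the cost of a useless score are shown.

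Third, the gain depends on the model. A modified Poisson model with the score and four hospital indicators, at 50 per group, gave 55%, 58% and 59% against 54%, 53% and 53% for chi-square: about 1, 5 and 6 points. With an uninformative score it fell from 56% to 51%. This stands, and is a reason to take the test from the logistic model.

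Fourth, a reader might infer that randomisation ignored hospital. The article does not show this. Its wording on an arrangement for the five hospitals can be read as allocation within each hospital, and it rules out only stratifying by procedure volume or teaching status. The chance of an uneven split within a hospital could be computed only by assuming simple randomisation, which is not stated.

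Fifth, the shortage of power comes from the sample size, not from the analysis. That is so, and adjustment is no substitute for correcting it. The gain would persist with a correct size, however: at 97 per group, adjusted power was 85%, 88% and 92% at AUC 0.70, 0.76 and 0.81, against about 80% unadjusted.

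Finally, an analysis plan that is not shown may hold a supportive adjusted analysis. The point therefore concerns only the primary analysis that the article fixes.

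**Conclusion.** The point holds as one about efficiency. The primary analysis is an unadjusted two-by-two comparison in a disease that the protocol itself calls heterogeneous, with a severity score normally available before randomisation. Adjusting for that score would add roughly 3 to 12 points at 50 per group to a true power of about 50 to 55%, if SOFA has an AUC of about 0.70 to 0.81 for death. The runs at 47 per group showed somewhat more, 6 to 15 points. With a weak score (AUC 0.63) the gain is 2 to 3 points.

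The documents do not support going further. No setting tried at AUC up to 0.86 restored 80% power at 47 per group (the highest was 72%), adjustment for hospital alone adds little, and the crude test is not biased. Whether allocation was by hospital is unclear from the article and should be stated.

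**What to change.** - Make the primary analysis a logistic model for in-hospital death with treatment and the last SOFA before randomisation. Take the test of treatment from this model, and standardise its predictions to a marginal relative risk with 95% CI, so that the planned effect measure is kept. State that the logistic test decides significance, since it and the interval can disagree near the boundary.
- Set a simple rule for missing baseline SOFA, for example imputation of the overall baseline mean without regard to arm, so that transferred patients stay in the intention-to-treat analysis.
- Keep the crude relative risk and chi-square test as supportive.
- State whether allocation was by hospital. If so, account for hospital in the primary model too.
- Correct the sample size calculation separately, and do not count the gain from adjustment towards it unless the assumed strength of SOFA is justified.

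The cost is wording in the analysis plan, fixed before outcomes by arm are seen. No new measurement is needed, but some baseline values may be missing. If SOFA proves not to be prognostic, the price is about 1 point of power with the logistic test, or about 6 if the test is based on the standardised log relative risk. With about 50 deaths expected in 100 patients (50 × 0.60 + 50 × 0.40), the model can carry one covariate.

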### Primary endpoint

The primary endpoint is mortality rate during the hospital stay for patients with acute pancreatitis.

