### Secondary endpoints

Secondary endpoints are duration time of organ failure, development of "new organ failure", number of infectious complications, necrosectomy, enteric fistulas, intensive care stay, and total hospital stay.

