### Data collection and follow-up

This study is coordinated by Emergency Surgical Department, Clinical Center of Serbia and School of Medicine, University of Belgrade. The clinical data of all randomized patients will be collected centrally in a database at the Emergency Surgical Department, Clinical Center of Serbia and School of Medicine, University of Belgrade. Trial coordinator will be in regular contact with the participating centers and will monitor the data of the every randomized patient.

Patients will be monitored during their hospital stay. For both, primary and secondary endpoints, follow-up will be finished at hospital discharge or death. Routine follow up visit are planned 3 and 6 month after discharge, including physical examination, abdominal ultrasound and/or CCT and/or MRI examination, to exclude presence of incisional hernias and pancreatic pseudocyst or other post-pancreatitis complications.

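### Ending endpoint follow-up at discharge implies that the supplementary Kaplan-Meier/log-rank analysis censors survivors at discharge, although discharge alive is a competing event for in-hospital death

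*Protocol article*

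**What the plan says.** All references are to the protocol article.

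- **Primary endpoint:** "The primary endpoint is mortality rate during the hospital stay for patients with acute pancreatitis".
- **Data collection and follow-up:** "For both, primary and secondary endpoints, follow-up will be finished at hospital discharge or death". The same section adds: "Routine follow up visit are planned 3 and 6 month after discharge". Those visits look for hernias, pseudocysts and other late complications and lie outside endpoint follow-up.
- **Statistical analysis, primary comparison:** "The comparison will be expressed in terms of relative risk and 95% confidence intervals", and "The research hypothesis will be evaluated by Fisher's exact test or Hi-square test (where appropriate), with a two-sided 0.05 significance level".
- **Statistical analysis, supplementary comparison:** introduced as an addition to the above, "survival probabilities over time will be estimated by Kaplan-Meier method and groups will be compared using the long-rank test". No time horizon and no rule for patients discharged alive is given.
- **Secondary endpoints:** the list includes "intensive care stay, and total hospital stay", so the trial allows that discharge times may differ between arms.

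**The concern.** If endpoint follow-up stops at discharge, a survivor's record for the mortality analysis ends that day, and a standard Kaplan-Meier analysis treats the end of a record without an event as censoring. The method then assumes that those who left would have gone on dying at the rate of those still in hospital. Patients are generally discharged because they have recovered, and once discharged they cannot die in hospital. Discharge alive is therefore a competing event, not non-informative censoring.

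Two consequences follow. The curves read higher than the proportion who actually die in hospital. And if survivors in one arm go home sooner, that arm's risk set shrinks faster and its later deaths carry more weight, so the log-rank test leans against it. Survival curves are prominent in a report of a mortality trial, and here they could disagree with the primary relative risk for reasons that have nothing to do with who died.

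**Working it through.** **Does the bias follow from the two rules?** Take an arm of n patients. First d1 die, then c are discharged alive, then d2 of those remaining die.

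- Actual in-hospital mortality: (d1 + d2)/n.
- Kaplan-Meier with censoring at discharge: 1 − [(n − d1)/n] × [(n − d1 − c − d2)/(n − d1 − c)] = d1/n + (d2/n) × (n − d1)/(n − d1 − c).
- Excess: (d2/n) × c/(n − d1 − c).

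The excess is positive whenever anyone dies after others have gone home. It grows with the number discharged before the late deaths, and is close to zero if nearly all deaths precede the discharges.

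**How large could it be?** The plan gives no figure for this analysis, so there is none to reproduce. From the article: 50 randomised per arm, and mortality of 60% and 40% (Sample size calculation, which anticipates that laparotomy "will lead to a mortality rate reduction from 60% of patients to 40" per cent). Assumed, because the article gives no time distributions: exponential times to death; gamma lengths of stay for survivors (shape 4); the means shown below. Each rejection rate rests on at least 3,000 simulated trials, so the Monte Carlo standard error near 5% is at most √(0.05 × 0.95/3000) ≈ 0.4 percentage points.

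*Equal true mortality of 50% in both arms, 50 per arm.* Actual mortality by day 60 is 0.5 × (1 − e^(−60/m)), where m is the mean time to death: 50%, 49% and 47.5% for m = 7, 14 and 20 days.

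| Mean time to death | Mean survivor stay | Actual day-60 mortality (both arms) | Kaplan-Meier day-60 mortality | Log-rank rejection at nominal 5% |
|---|---|---|---|---|
| 7 days | 50 vs 30 days | 50% | about 51% vs 54% | about 5–6% |
| 14 days | 50 vs 30 days | 49% | about 53–54% vs 68% | about 8–10% |
| 20 days | 50 vs 30 days | 47.5% | about 53–54% vs 70% | about 13% |
| 14 days | 40 vs 40 days | 49% | about 57–58% in both | about 5% |

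Nearly all the excess rejections at 14 and 20 days go against the arm discharged earlier. Smaller gaps matter less: at a mean time to death of 14 days, stays of 40 vs 35 days give 4.9–5.4%, and 45 vs 35 days give 5.7–6.5%. At the other extreme, 60 vs 20 days with a mean time to death of 20 days gives 41%.

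*Mortality of 60% vs 40%, mean time to death 14 days, 50 per arm.*

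| Handling of discharge | Log-rank power |
|---|---|
| Censored; lower-mortality arm leaves earlier (30 vs 50 days) | about 26% |
| Censored; lower-mortality arm leaves later (50 vs 30 days) | about 70% |
| Discharged patients kept event-free in the risk set | about 51% in both cases |

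The 51% is below the plan's 80% because 50 per arm gives only about 52% power for 60% vs 40% by the usual two-proportion calculation. That is a separate matter; the present point does not depend on it.

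**The case against.** The strongest reply is that the article never says survivors are censored at discharge. It fixes an end of follow-up and names a method. Discharged patients could be carried event-free to a common horizon, which holds the test near 5%, and censoring rules are usually left to a full protocol or analysis plan not shown here. It is right that the censoring is implied, not stated. But the point is not the missing rule: the article states both the end of follow-up and the method, and applied in the ordinary way they do not fit together. An analysis plan that kept both would inherit the problem.

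Three further replies stand and limit the point.

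- The comparison is supplementary. A reader might infer that the primary result is biased. It is not: the relative risk and the Fisher or chi-square test use the proportion who die in hospital and are untouched by censoring at discharge.
- A reader might infer that a particular arm will be disadvantaged, since one has an open abdomen with reoperations and the other a catheter. The article predicts no difference in survivors' stay, and day 9 is a reference point for closure in one arm and catheter removal in the other. The direction is unknown.
- A reader might infer that the log-rank test must be seriously distorted. If deaths come early or stays are similar, it hardly moves. It also remains a valid test of the hazard of death while in hospital; that hazard is simply not the quantity the primary endpoint asks about.

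**Conclusion.** The concern holds for the supplementary survival analysis only. Read together, the two stated rules imply censoring at discharge, and the Kaplan-Meier curves would then overstate in-hospital mortality even when the arms have equal stays. The log-rank test is affected only if survivors' discharge times differ between arms, and it then leans against the arm discharged earlier.

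The size rests wholly on assumed times to death and stays. For mean stays of 50 and 30 days it runs from negligible, when deaths average 7 days, to an overstatement of about 22 percentage points in the earlier-discharged arm (70% against 47.5%) and a false-positive rate near 13%, when deaths average 20 days. Under the planned mortality difference, the same gap in stay could roughly halve the log-rank test's power or raise it well above its proper level, depending on which arm leaves first. This is worth correcting before analysis, but it does not threaten the primary comparison.

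**What to change.** **Preferred.** Replace the Kaplan-Meier/log-rank comparison with the cumulative incidence of in-hospital death, treating discharge alive as a competing event, compared by Gray's test. Equivalently, keep discharged patients event-free in the risk set up to a stated fixed horizon. Either way the curve leads to the crude in-hospital mortality on which the primary relative risk is based. This needs only a change of analysis wording, because dates of death and discharge are already needed for the stated endpoints.

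**If Kaplan-Meier and log-rank are kept.** Define the event as all-cause death from randomisation to a fixed day 90, with discharged patients remaining at risk. Vital status can be confirmed at the visit planned 3 months after discharge, which for discharged patients falls at or after day 90 from randomisation. State that this is a different estimand from in-hospital mortality and is supportive only. The cost is a protocol change that brings vital status at that visit into endpoint follow-up, and a way to establish it for patients who do not attend.
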